**Phase 2**

Power Calculation: In preparation for this proposal, baseline use of hypoglycemia-prone medications (e.g., sulfonylureas, mealtime, or mixed insulin) was evaluated in 3921 KPNC patients identified as “high risk” by the KPNC hypoglycemia risk tool. Among these patients, 75% were on hypoglycemia-prone treatment. Approximately 60% of the intervention arm and 20% of the usual care arm will be prescribed safer diabetes regimens within 6 months compared

to baseline. The minimum number of subjects needed to detect this 40% absolute difference, assuming 90% power and a 10% attrition rate, is 86 patients (43 per arm). With an enrollment size of 200 (100 per arm), this trial is more than adequately powered to detect the hypothesized difference.

- Any procedures that will be used for quality control of collected data.

Data analysts routinely inspect the data for corrupt fields or extreme outliers.

c. Sharing of Results with Subjects

Describe whether results (study results or individual subject results, such as results of standard or research lab tests and genetic tests) will be shared with subjects or their providers and under which circumstances.

N/A

If the study carries a risk of incidental findings, describe your plan for evaluating these and determining whether and how subjects or their providers will be given this information.

N/A

If laboratory results will be shared with subjects or their healthcare providers, verify that the laboratory conducting the test is Clinical Laboratory Improvement Amendments (CLIA) certified.

N/A

Describe how study participants will be updated on research progress via newsletter, summary, etc. Consider incorporating such updates to study participants as part of ongoing retention efforts.

N/A

## **10. Privacy, Confidentiality and Data Security**

Describe the steps that will be taken to protect subjects' privacy during recruitment, consent and study procedures.

Usual care procedures for protecting patient privacy will be used.

Describe the plan for storage of data and/or biospecimens including:

- Who will have access?

The PI, Co-I's and study team will have access to identifiable information from the medical record and other clinical databases. PHI will not be disclosed outside of study team.

- Where the data/materials will be stored and for how long. Indicate if data will be encrypted and password protected and if transportable/removable media will be used. Indicate if data will be stored on non-KP devices or sponsor-provided devices.

Data will be stored in password protected or encrypted electronic files and stored on protected KPNC servers within KP network secured by firewalls. Passwords will not be disclosed to any party

not involved in the study. Patient identifiers will not appear in any part of the publications. When it is necessary to share PHI information among study parties within KPNC, password-protected/encrypted files will be transmitted through encrypted KPNC email or secure file transfer. The information will be stored for the length of the project and destroyed after the final manuscripts are published. Data will be NOT stored on non-KP devices or sponsor-provided devices.

- If applicable, how will data be transmitted? (e.g. Encrypted email, secure file transfer, sponsor provided site)

Data will be transmitted via password-protected/encrypted files through encrypted KPNC email or secure file transfer.

- What identifiers will be included.

MRNs, dates

- Any other steps that will be taken to ensure security (e.g., training of staff, authorization of access, password protection, encryption, physical security, and separation of identifiers from data and specimens, certificates of confidentiality).

None, the investigators believe that the plan to protect the data is appropriately mitigated.

- Describe the plan to destroy/archive or retain data at the end of the study. If storing information and/or identifiable biospecimens for future research, complete the next section.

Personal identifiers associated with participants will be destroyed as soon as possible after the study has finished and after publication of all manuscripts. Since manuscript submission and revision process often requires re-access of patient information, patient identifiers will be kept until all publications generated from the study have been finished, at which time all patient identifiers will be destroyed at the close of the study.

## **11. Information and/or Biospecimen Banking for Future Research**

If you are creating a repository, please submit a separate protocol.

Indicate if biospecimens may be used for future research and whether that may include genetic research.

N/A

State if information or biospecimens will be sent to a separate repository. If data or specimens will be banked in a repository for future use as part of this protocol submission address the following questions:

- What will be banked and what identifiers will be associated with the information or biospecimens?

N/A

- Where and how will the information or specimens be stored?

N/A

- For what purpose will the information or specimens be used? Include a general description of the types of research that may be conducted with the identifiable private information/biospecimens (e.g. research on cancer).

N/A

- How will the information or specimens be accessed, and who will have access?

N/A

- Describe the procedures to release information or specimens, including the process to request a release, approvals required for release, who can obtain information or specimens, and the information to be provided with specimens.

N/A

- How long will identifiable private information/biospecimens be stored?

N/A

## **12. Collection of data from subjects electronically**

If you will collect any data from participants electronically (including email, website, etc.), explain:

- Does the study involve a Mobile Device or Application? If yes, please indicate the source/manufacture/developer of the product:

No.

- How and what data will be collected. Indicate if PHI is collected electronically (including via an app) and if there is any interface with the subject's personal accounts (for example: if subjects need to create an account to use the device, or if the device interfaces with an external source of data, or medical record).

N/A

- How the information will be secured/transmitted/stored (encryption, password protection, etc.; may require consultation with IT department). Include a data flow diagram if data will flow through multiple parties (such as a hosting provider or coordinating center).

N/A

- Any risks to the participants' privacy posed by using these methods (describe in consent, as applicable).

N/A

- Describe if email containing PHI will be used to communicate with participants? (Per KP policy, securing messaging must be used for all communications containing PHI.)

N/A

- How you will verify the participant's identity.

N/A

### **13. Disclosure of PHI to a collaborator**

If any data will be sent outside of this site, list each recipient (may list by role or category if the information is the same for several different entities). For each recipient, describe:

- The name and location of the individual/entity receiving the information.

N/A

- What information and/or biospecimens will be sent.

N/A

- Whether the information will be fully identifiable (PHI, if health information), a Limited Data Set, de-identified, or aggregate.

N/A

- How the data/materials will be transferred securely (for instance, Secure File Transfer). Indicate if hard copy PHI will be stored/sent to a collaborator.

N/A

- When applicable, clarify whether there are written assurances from collaborators that PHI will not be reused or re-disclosed to any other entity. Describe assurances that PHI will be stored securely. Describe mechanisms (e.g., intrusion detection software or regular electronic system activity audits or monitoring) for determining if KP PHI has been inappropriately or illegally accessed, used, disclosed, or modified.

N/A

### **14. Provisions to Monitor Data to Ensure the Safety of Subjects**

This is required when research involves more than Minimal Risk to subjects.

The plan might include establishing a data monitoring committee and a plan for reporting data monitoring committee findings to the IRB and the sponsor. Describe:

- Who will monitor the study data for safety?

N/A. This study involves no more than minimal risk to subjects.

- The plan to periodically evaluate the data collected regarding both harms and benefits to determine whether subjects remain safe.

N/A

- What data are reviewed, including safety data, untoward events, and efficacy data.

N/A

- How the safety information will be collected (e.g., with case report forms, at study visits, by telephone calls with participants).

N/A

- The frequency of data collection, including when safety data collection starts.

N/A

- The frequency or periodicity of review of cumulative data.

N/A

- Criteria for taking action on monitoring findings (for instance, stopping rules, immediate suspension, reporting, protocol changes, changes to monitoring frequency or plan).

N/A

- For studies monitored by a DSMB/C, describe the committee membership and structure, meeting format, and quorum requirements. Upload the board/committee charter, if one exists.

N/A

## **15. Risks and Benefits**

### **a. Risks to Subjects**

List the reasonably foreseeable risks, discomforts, hazards, or inconveniences to the subjects related the subjects' participation in the research. Consider physical, psychological, social, legal, and economic risks.

No foreseeable risks, discomforts, hazards, or inconveniences to participants are anticipated.

Describe the probability, magnitude, duration, and reversibility of the risks.

N/A

If applicable, indicate which procedures may have risks to the subjects that are currently unforeseeable.

N/A

If applicable, indicate which procedures may have risks to an embryo or fetus should the subject be or become pregnant.

N/A

If applicable, describe risks to others who are not subjects and risks to Kaiser Permanente

N/A

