### 3. Background

#### a. Scientific Background

Provide the scientific or scholarly background for, rationale for, and significance of the research based on the existing literature and how will it add to existing knowledge. A list of references or bibliography must be included as part of this document or uploaded separately.

Hypoglycemia in patients with type 2 diabetes (T2D) is a significant adverse drug event associated with the hypoglycemia-inducing diabetes medications, insulin and sulfonylureas. Hypoglycemia has been poorly addressed by health plans and all but ignored by national performance metrics such as HEDIS.

Hypoglycemia is common (in a survey of 20,188 diabetes patients from KPNC, 12% reported having  $\geq 1$  severe hypoglycemia events requiring third-party assistance in the previous 12 months), morbid (associated with falls, fall-related fractures, automobile accidents, cardiovascular events, dementia, and even death), and costly (total annual direct medical costs ~\$1.8 billion in 2009 in the US). Hypoglycemia often leads to significant diabetes distress and nonadherence to prescribed diabetes medications. Providers are challenged to address the competing demands of prescribing glucose-lowering medications to meet glycemic targets while avoiding hypoglycemia.

In addition, there are now strategic considerations for reducing hypoglycemia risk. NCQA is proposing a new HEDIS measure assessing emergency department visits for hypoglycemia in older adults with diabetes for measurement year 2023 (MY2023). There is little time to prepare before its proposed implementation in 2023. Unlike most of the existing HEDIS measures, this new measure is focused on patients  $>65$  years of age and is not capped at 75 years of age, which matches the age range where hypoglycemia risk is highest. Hypoglycemia risk can be mitigated, but there exist no well-validated, population management approaches for hypoglycemia prevention. Our proposal intends to address this gap by developing and evaluating a practical population management approach to hypoglycemia prevention.

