**Phase 2**

In **Phase 2** of this study (Aim 3), the investigators will:

- conduct a prospective evaluation of whether proactive intervention by the Hypoglycemia Champion (augmented usual care) is associated with better diabetes regimen safety among KPNC members at high risk of hypoglycemia compared to usual care (control) [Aim 3].

**Aim 3 –Conduct a prospective evaluation of whether proactive intervention by the Hypoglycemia Champion APM (i.e., assignment to augmented usual care group) is associated with better diabetes medication regimen safety among KPNC members at high risk of hypoglycemia compared to usual care (control).**

- Randomly assign eligible patients to receive proactive intervention by the HC APM (augmented usual care group) for comparison to data-only patients receiving usual care. All eligible patients will be managed according to the regionally disseminated HOAP as new standard of care). All medical decisions for all patients (augmented usual care and usual care) are made by each member’s medical care team responsible for his or her care (not by study personnel).
- **Primary Outcome:** Proportion of high-risk patients prescribed safer diabetes regimens (discontinuation at 6 months compared to pre-baseline of sulfonylureas, mealtime [rapid-/short-acting], or mixed insulin) comparing study participants (augmented usual care) to data-only patients (usual care controls). The study hypothesis is that more study participants will be prescribed safer diabetes regimens compared to data-only patients. Baseline pharmacy dispensing data and medication discontinuation orders during follow up will be collected directly from EHR/Clarity tables.
  - i. As researchers, patients will not be contacted directly at any time.
  - ii. All care will be delivered under approved protocols by KPNC clinicians.
  - iii. All evaluation data related to clinical outcomes will be collected directly from the medical record of usual care.
- **Secondary Outcomes:** the investigators will also examine differences between study participants and data-only patients in glucagon prescribing, CGM use, hypoglycemia on the

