**Phase 2**

There will be no recruitment. All patients will already be receiving usual care from an APM.

- For study participants, the HC will communicate with each participant's provider (usual APM or physician) to coordinate care; the study participant will receive proactive intervention by the HC as an augmentation to their usual care.
- For the data-only patients, there will be no contact.

Indicate whether you will openly recruit using advertisements, websites, flyer, or brochures. (Upload the final versions of all recruitment materials to your submission to the IRB.)

N/A

Indicate if you plan to do targeted recruitment using existing records or referral. Please submit final versions of all referral emails/scripts.

N/A

Describe, by position/title, who will be recruiting and enrolling participants (providing the specific names of research team members is not necessary).

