**Phase 2**

Study participants will receive augmented usual care from the HC APM (whose goal is to fully implement the new standard of care protocol with the intention of reducing the risk of hypoglycemia and improving safety). The attention presents no more than minimal risk to participants. (Data-only patients are not research subjects; they will receive usual care from their regular APM; the study will have no direct contact with the data-only patients.)

- Explain how the waiver of informed consent will not adversely affect the rights and welfare of the participants.

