**Phase 2**

APM will routinely monitor study participants for safety and report any concerns to the Investigator.

- Procedures performed to lessen the probability or magnitude of risks.

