**Phase 2**

Data collected from study participants and data-only patients

- Prescribing orders and pharmacy dispensing of medications including
- Durable medical equipment orders and dispensing of continuous glucose monitor devices and supplies
- Relevant lab results (e.g., HbA1c)
- ED visits or hospital admissions for hypoglycemia
- Hypoglycemia on the problem list
- Visit notes

- The duration of an individual subject's participation in the study.

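### Acute hyperglycemia events are not collected or analysed in either arm, and the only between-arm check on loss of glycemic control is HbA1c below 8% with no margin

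*Supplement*

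**What the plan says.** All references are to the latest protocol version in the Supplement, dated January 27, 2025.

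- **Primary outcome (section 4, Phase 2, Aim 3).** A safer regimen is defined as "discontinuation at 6 months compared to pre-baseline of sulfonylureas, mealtime [rapid-/short-acting], or mixed insulin". Section 9b expects this in about 60% of the intervention arm and 20% of the usual-care arm.
- **Trade-off (section 3a).** The background says "Providers are challenged to address the competing demands of prescribing glucose-lowering medications to meet glycemic targets while avoiding hypoglycemia". Section 4 then hypothesises that glycemic control, measured as HbA1c below 8%, will be stable.
- **Events collected (section 9a).** The only acute events in the list for both groups are "ED visits or hospital admissions for hypoglycemia". The list also includes laboratory results such as HbA1c, and visit notes.
- **Analysis (section 9b).** The between-arm secondary comparisons are hypoglycemia emergency visits or hospitalizations within 6 months, CGM and glucagon prescribing, and the proportion with HbA1c below 8%.
- **Risk statement (section 15a).** "No foreseeable risks, discomforts, hazards, or inconveniences to participants are anticipated".

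**The concern.** The intervention is meant to increase the number of patients who come off certain glucose-lowering drugs, and the primary outcome scores each discontinuation as a gain in safety. That outcome cannot register harm from the discontinuation itself. The opposing harm is loss of glycemic control, which the plan recognises, and its acute form is an emergency visit or admission for hyperglycemia. The plan counts the acute event that the intervention should reduce and leaves out the one that it might increase.

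The trial could therefore report safer regimens and fewer hypoglycemia admissions with no count of hyperglycemia admissions beside them. HbA1c below 8% is the only safeguard, and it is coarse. A patient already above 8% who deteriorates further does not change the proportion. With no margin stated, failure to find a difference could be read as stability.

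**Working it through.** **Inputs from the plan.** 100 per arm; 10% attrition (so about 90 per arm in a worse case); expected discontinuation 60% vs 20%; 90% power; stated minimum 43 per arm.

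**Assumptions, because the plan gives no figures.** Control-arm hyperglycemia event rate over 6 months of 1%, 2% or 5%; control-arm proportion with HbA1c below 8% of 50% to 80%; two-sided alpha 0.05.

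**1. The plan's own sample-size figure.** With the pooled normal approximation, n = [1.96·√(2·0.4·0.6) + 1.2816·√(0.24 + 0.16)]² / 0.4² = 30 per arm, and 30/0.9 rounds up to 34. The plan's 43 is not reproduced at this alpha (the plan states none), but it is the more cautious figure. Power at 100 per arm exceeds 99.9%. The size is ample for the primary outcome and says nothing about harm.

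**2. Size of the planned change.** 60 − 20 = 40 more patients per 100 discontinuing in the intervention arm, on the plan's own expectation.

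**3. Acute events, by direction.**

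| | Hypoglycemia | Hyperglycemia |
|---|---|---|
| Secondary outcome (section 4) | yes | no |
| Collected in both arms (section 9a) | yes | no |
| Compared between arms (section 9b) | yes | no |

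**4. What the HbA1c comparison can show.** The 95% half-width for the difference is 1.96·√(2p(1−p)/100).
- p = 50%: 1.96·√0.0050 = 13.9 points
- p = 80%: 1.96·√0.0032 = 11.1 points

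The drop detectable with 80% power is 18 to 20 points across this range. A non-significant result is therefore compatible with a substantial loss of control.

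**5. What adding hyperglycemia events would give (100 per arm).**

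| Assumed control rate | Power for a doubling | Intervention rate detectable with 80% power |
|---|---|---|
| 1% | 8% | 10.0% |
| 2% | 13% | 12.1% |
| 5% | 27% | 17.5% |

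With zero events in 100, the one-sided 95% upper bound is 1 − 0.05^(1/100) = 3.0% (3.3% with 90). The upper limit of the two-sided exact 95% interval is 1 − 0.025^(1/100) = 3.6%.

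**The case against.** The strongest reply is that the plan does guard against loss of control. HbA1c below 8% is a named secondary outcome compared between arms, hypoglycemia events are compared in both arms, and laboratory results and visit notes are extracted for both. This stands. A reader might infer that harm cannot be compared at all, and the documents do not support that. What remains is that no acute hyperglycemia event is defined from those sources and that the HbA1c check has no margin. The HbA1c measurement window and missing-value rule are also not given, but an analysis plan commonly carries them, and they are not held against the protocol here.

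A reader might also infer three other things:

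- **That the study withdraws insulin.** Section 4 leaves decisions to each member's care team, the guideline applies to all eligible patients, and the outcome covers mealtime and mixed insulin, not all insulin.
- **That section 9a contradicts section 14.** Section 9a says "APM will routinely monitor study participants for safety and report any concerns to the Investigator", while section 14 answers "N/A. This study involves no more than minimal risk to subjects". The template requires section 14 only above minimal risk, and section 9a answers a different prompt about routine monitoring. The two can coexist.
- **That one-arm safety reports bias the comparison.** The reports do concern study participants only, and "For the data-only patients, there will be no contact". But nothing makes them an outcome or analysis variable, and outcome data come from the medical record for both groups.

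The background's mention of hyperglycemia admissions argues for the study's focus on hypoglycemia; it is not evidence of an expected excess.

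Finally, with power of 8% to 27% for a doubling, the added events would be descriptive. This stands too and limits what the fix can claim. It does not justify leaving the events uncounted, since without them no bound can be reported.

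**Conclusion.** The point holds as stated in the heading. Acute events are counted in the favourable direction only, in a trial that expects about 40 more discontinuations per 100 patients in the intervention arm. The one planned between-arm check on control carries an interval of about ±11 to 14 points and no margin, so it cannot by itself support a statement that control was stable. These widths rest on assumed control proportions of 50% to 80%. The event-rate figures rest on assumed rates of 1% to 5%, because the documents give none.

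The conclusion is confined to a missing outcome and an unsupported inference. It is not a finding that the intervention is harmful, that safety is wholly uncompared, or that the monitoring sections conflict. The unqualified risk statement in section 15a does sit uneasily with the trade-off in section 3a and the glycemic-control hypothesis in section 4, and these passages need to be reconciled.

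**What to change.** 1. **Sections 4, 9a and 9b.** Add emergency visits or hospitalizations with a primary diagnosis of hyperglycemia, including hyperglycemic crisis, to the same electronic-record extraction, for both arms and over the same 6 months as the hypoglycemia events.
2. **Reporting.** Give counts per arm and the between-arm difference with exact 95% confidence intervals, next to the hypoglycemia events. State in advance that this comparison is descriptive and that 100 per arm cannot exclude a modest excess.
3. **HbA1c below 8%.** Report the difference with its confidence interval and do not conclude stability from a non-significant test unless a margin has been set beforehand.
4. **Section 15a.** Reconcile the risk statement with sections 3a and 4. No treatment rule is proposed.

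The changes should be fixed before the arms are compared. The cost is a few extra diagnosis codes in an existing extraction, an IRB wording change and a slightly less favourable risk statement. No added patient contact, staff or procedure is needed; for the controls this respects the commitment that "the study will have no direct contact with the data-only patients".
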